## Abstract

**Background:**

Visual impairment caused by cataracts not only affects an individual's quality of life but can also have a profound impact on other important psychological factors and on the economic circumstances of individuals and their households. Cataract surgery is an effective intervention to restore vision and is also associated with other positive consequences including improvements in quality of life, economic and psychological outcomes. While there has been an increase in the number and quality of cataract surgeries performed in Vietnam, the programs currently in place are still unable to meet the existing demand and need for surgery. Data on both the cost-effectiveness of cataract surgery and the economic and psychological impact of untreated cataract in this setting is lacking.

**Methods/Design:**

This study, investigating the psychological and economic impact of cataract surgery in Vietnam (VISIONARY), will recruit and interview a sample of adults (18 years or over) who are referred for cataract surgery by one of the following sites and their outreach programs: Hue Eye Hospital; Thai Binh Eye Hospital; Binh Dinh Department of Health Eye Hospital and the Vinh Long Department of Health Social Disease Centre. All participants (those who have cataract surgery and those who do not have surgery) will be followed up at six and 12 months.

**Discussion:**

This study is designed to examine the impact of low vision on household economic circumstances and psychological outcomes as well as to investigate the effectiveness and cost-effectiveness of cataract surgery in Vietnam. It will help to inform international and national non-government organisations working in the country and local policy-makers on priorities for further investment in eye-health services in this setting and their relevance to broader economic development goals.

## Background

Vietnam has a population of 86 million people, of which over two-thirds are between the ages of 15 and 65 years and approximately 5% are over the age of 65 years [1]. While an improving economy over the last few decades has resulted in the creation of new employment opportunities and a dramatic decrease in poverty rates [1], ill-health and poor access to necessary and timely health care continue to pose a threat to the economic wellbeing of individual households and the on-going economic development in this country.

Cataract is the leading cause of blindness in Vietnam, affecting 87.6 new cases per 100,000 each year and causing approximately 65% of all blindness [2]. There is currently a very high prevalence of blindness, affecting 4,034 people per 100,000 [3]. Of even more concern is the staggering numbers who are living with low vision, approximately 18,086 people per 100,000, much of which is caused by untreated cataract [3].

Visual impairment is defined according to the ICD 10^th ^revision 1^st ^and 2^nd ^edition as a visual acuity that is less than 6/18 (equivalent to 3/10) but equal to or better than 3/60, or a corresponding visual field loss of less than 20 degrees in the better eye with best possible correction. Low vision can negatively affect an individual's quality of life [4] and it can also have an impact on other psychological factors such as emotional wellbeing [5]. Furthermore, like other chronic illnesses, vision impairment can have profound economic effects on individuals and their households. This is particularly the case for those from socioeconomically disadvantaged groups and for people with severe disability. As a consequence, chronic illness can be a major cause of poverty due to the impact it has on productive activities such as work, education and caring. In low-income countries such as Vietnam, the economic effects of vision impairment due to cataract can be particularly catastrophic given the absence of social security safety nets.

Cataract surgery has been shown to be effective in restoring vision [4,6] and as a consequence improvements in quality of life, economic and psychological outcomes should to be experienced relatively quickly [5,7,8]. Furthermore, when conducted as part of a regional program, it represents a potentially low cost, high impact intervention that can potentially be rolled out across low income high prevalence settings. There are several international organisations working with local service providers in seeking to improve eye care in Vietnam. The Fred Hollows Foundation, a non-profit international development organisation involved in blindness prevention operates The Vietnam Blindness Prevention Program in ten provinces in both rural and urban areas in Vietnam. This program has contributed to increasing the number and quality of cataract surgeries performed in Vietnam each year. In 2009, the program screened 810,148 people and performed 27,331 sight restoring or improving interventions, which included 11,383 cataract surgeries. ORBIS is another non-profit organisation that is working to eliminate avoidable blindness in the region. In 2008 they screened over 900,000 people and as a result, were able to offer non-surgical ophthalmic medical treatments to over 96,000 people and perform over 26,000 eye surgeries in Vietnam [2].

While there has been an increase in the number and quality of cataract surgeries performed in the last few decades, the programs currently in place are nonetheless still unable to meet the existing demand and need for surgery in Vietnam. A 2009 study of the impact of resources and socioeconomic factors on eye care and blindness prevention, conducted by the Health Strategy and Policy Institute of Vietnam, concluded that a national strategy and action plan for blindness prevention was urgently required and that current networks, training, facilities and budgets were insufficient to meet the current need [9]. Data on both the cost-effectiveness of cataract surgery and the economic and psychological impact of untreated cataract will help to inform priority-setting, health care planning and further investment in eye-health services in this country.

This study will examine the household economic impact and psychological outcomes associated with low vision and will investigate the cost-effectiveness of cataract surgery.

## Methods/Design

### Overview

This is a prospective study of individuals who are referred for cataract surgery (Figure 1). The primary aim is to determine the impact that cataract surgery has on quality of life, visual function, household economic circumstances and psychological outcomes. This study will also investigate the cost-effectiveness of cataract surgery.

**Figure 1 F1:**
[figure not shown]
**VISIONARY study design**.

### Study population

Men and women aged 18 years and older will be eligible to participate in this study if they fulfil the following criteria:

• Receive a referral for cataract surgery, based on a clinical assessment of their best corrected visual acuity for both eyes

○ Visual acuity measured as 3/10 or worse in the better eye

The exclusion criteria are as follows:

• Previous surgery performed to remove a cataract in either eye;

• Another illness of the eye that reduces vision (other than a cataract; does not include blindness caused by injury);

• Unable to participate in two follow up appointments.

### Recruitment

Eye health service providers from each of the participating regions travel to regional areas several times per year to screen people living in the region for vision impairment. Individuals who are screened and referred for cataract surgery will be invited to participate in this study. The eye health service providers will provide eligible individuals with information about the study and ask them if they are interested in joining. Potential participants will be informed that the decision to take part in the study is voluntary, that they are free to withdraw from the study at any time and that whatever their decision, it will not affect their medical treatment or their relationship with the eye health service providers. Individuals who indicate an interest in participating in the study will be referred to the research staff who will obtain written informed consent.

Participants will also be recruited by private health centres that perform cataract surgery in all four regions. Individuals who elect to have the surgery performed privately will present directly to these private health centres. This recruitment strategy will capture the diversity of participants who are living with vision impairment in the regions. To ensure sufficient representation of participants from low socio-demographic backgrounds, the study will only recruit a maximum of one private participant for every participant recruited from the vision outreach programs.

### Study sites

Participants will be recruited from outreach screening programs coordinated by the following sites: Hue Eye Hospital; Thai Binh Eye Hospital; Binh Dinh Department of Health Eye Hospital and the Vinh Long Department of Health and Social Disease Centre.

*Hue Eye Hospital *is located in Thua Thien-Hue, in the Central Region of Vietnam. It has one main city and eight districts and a population of 1.1 million people. The main industries in the region include: tourism, agriculture, forestry and fishing.

Blindness is estimated to affect 1% of the population in this region, with approximately 1,130 new cases per year. 2,200 cataract surgeries are performed in the region per year.

*Thai Binh Eye Hospital *is located in the city of Thai Binh, which is in the Red River Delta, 60 km away from the capital city, Hanoi. Thai Binh has a total population of 1.9 million people. The province is composed of Thai Binh city, and 7 districts. Agriculture is the main industry - 80% of the population are farmers according to national statistics.

Approximately 0.63% of the population are blind or have low vision. In 2009, there were a reported 8,658 people with bilateral blindness and 24,000 people with unilateral blindness due to cataract who needed surgical treatment. About 2,000 cataract surgeries are performed each year in the province.

*Binh Dinh Department of Health Eye *is located in Binh Dinh, in the centre of Vietnam. It has a population of 1.5 million people, most of whom work in the farming or fishing industry.

The leading causes of blindness in the province are cataract, cornea lesions, glaucoma, eye trauma or injury and refractive error. The increasing rate of non-infection eye diseases is one of the challenges of the eye care sector in the province. About 1.1% of the population or 17,400 people are blind. In addition, 7.3% of the population have a visual acuity lower than 1/10. The number of cataract surgeries performed in the region has been steadily increasing in the last three years, with 1,587 surgeries performed in 2008, 1,977 in 2009 and 2,808 in 2010.

*Vinh Long Department of Health Social Disease Centre *is located in Vinh Long, in the Mekong delta; around 120 km away from Ho Chi Minh City. It has a population of 1.1 million people, 57% of whom are farmers.

Approximately 0.63% of the population are blind due to cataracts. The province has eight eye doctors, four of whom are in charge of outreach activities and the remaining four perform treatment activities only.

### Assessments and data collection

The detailed schedule for data collection is shown in Table 1. The interview schedule was developed in English and incorporates questions and tools that have been validated for use in Vietnamese. The full interview schedule has been translated into Vietnamese for administration and piloted with research staff in Vietnam.

**Table 1 T1:** Schedule of assessments in the VISIONARY study

Participant assessment	Baseline	6 months	12 months
Initials	✓		

Full name	✓		

Date of birth	✓		

Contact information	✓		

Next of kin	✓		

***Demographic characteristics***			

Sex	✓		

Age	✓		

Education	✓		

Marital status	✓		

Type of insurance	✓	✓	✓

Household head relationship	✓		

Household composition	✓		

***Employment***			

Main lifetime occupation	✓		

Time spent doing paid work	✓	✓	✓

Time spent doing unpaid work	✓	✓	✓

Impact of eyesight on ability to work	✓	✓	✓

Return to work (paid/unpaid)		✓	✓

Income support	✓	✓	✓

***Household economic situation***			

Annual income	✓	✓	✓

Main source of income	✓	✓	✓

Estimated value of assets (non-livestock and live-stock)	✓	✓	✓

Asset ownership	✓	✓	✓

Financial assistance	✓	✓	✓

***Medical information***			

Visual acuity (in both eyes)	✓	✓	✓

Cataract location	✓	✓	✓

Year of onset of visual impairment	✓		

Co-morbidity	✓	✓	✓

Impact on family carer	✓	✓	✓

Complications from cataract surgery		✓	✓

Visual acuity (in both eyes)	✓	✓	✓

***Health service use***			

Date assessed for cataract surgery	✓		

Date of cataract surgery	✓		

Type of cataract surgery referral	✓		

Type of health service use and number of visits	✓	✓	✓

Out-of-pocket spending	✓	✓	✓

Intention to have cataract surgery	✓	✓	✓

Post-surgery complications		✓	✓

***Quality of life***			

Health related quality of life - SF 12v2 [10]	✓	✓	✓

***Household economic hardship***			

Financial stress	✓	✓	✓

Use of financial coping strategies	✓	✓	✓

Impact of illness on household income	✓	✓	✓

Subjective perception of household economic situation	✓	✓	✓

***Mood (psychological impact)***			

Self-reporting questionnaire (Vietnamese version) [11]	✓	✓	✓

***Screening and interview information***			

Location where consent was obtained	✓		

Interview location	✓	✓	✓

Date of interview	✓	✓	✓

#### Baseline interviews

The baseline interview will be administered in person at the outreach screening program or at the private health centre. Baseline interviews will assess demographic information, medical history, health service use, quality of life, economic circumstances and psychological outcomes. Contact details will be collected from participants at the baseline interview in order to schedule the six and 12 month interviews.

#### 6 and 12 month interviews

A follow-up assessment will be carried out six months and 12 months after the participant's scheduled date of surgery using a similar interview schedule to that administered at baseline. These interviews will be carried out face-to-face in participants' homes or at other locations of their choice. All participants will be followed up, including those who have not had surgery.

### Source of questions included in the assessment tool

#### Quality of life

The primary outcome, health-related quality of life, is measured using The Short Form 12 version 2 Health Survey (SF-12 v2), which includes a subset of questions from The Short Form 36 survey (SF-36). This is a generic tool that uses 12 questions to measure functional health and well-being across the following domains: physical functioning, social functioning, role limitations due to physical problems, role limitations due to emotional problems, mental health, energy and vitality, pain and general health perception [10]. The Vietnamese translation of the SF-36 found that all sub-scales demonstrated good discriminant validity and that the cultural factors specific to the Vietnamese population are not inconsistent with this tool [12]. The questions that correspond to the SF-12v2 will be used in this study.

#### Economic circumstances and health care utilisation

The secondary outcomes, which cover household economic circumstances and health care utilisation, are assessed via the following indicators: employment status; household income; household wealth; household economic hardship and health care utilisation.

To assess *employment status*, questions on time spent in paid and unpaid work for the participant are modified from questions 6-8, 12b and 26-27 from Section 4b of the 2006 Vietnamese Household Living Standards Survey [13]. The average number of hours of paid and unpaid work performed per week over the previous 12 months will be calculated. In addition, at six and 12 months participants are asked to indicate whether, and in what capacity, they have returned to work (paid and unpaid): same job, similar job, different job and the average number of hours worked per week. The date of return to partial or full-time work will be recorded.

The main source of *household income *is modified from questions 12(a-e) in Section 4b of the 2006 Vietnamese Household Living Standards Survey [13]. Participants are also asked about annual income and whether they are receiving any income support payments (sickness, disability, or unemployment payments provided by the Government) or health-insurance benefits.

*Household wealth *is measured using questions that cover key aspects of socioeconomic well-being including details of the dwelling construction and ownership and value of a small number of assets and will be combined into an index of household wealth [14].

*Household economic hardship *will be determined by a series of questions about failure to pay basic living and medical expenses and whether there was help provided by any organisation or individual to meet these payments. An advantage of this measure is that it is sensitive to the possibility that individuals prioritise certain payments (e.g. forgo medical expenses to pay school fees). The basis for these questions comes from the US Census Survey of Income and Program Participation [15] and a modified version has been used in the authors' previous work [16-18]. Economic hardship will be constructed as a dichotomous variable where a reported inability to make any one of the payments posed to respondents will be classed as a case of economic hardship.

*Health service utilisation *and the associated out-of-pocket expenditure for both health and non-health categories is collected using a modified version of Questions 8-12 from Section 3a of the 2006 Vietnamese Household Living Standards Survey [13]. The out-of-pocket burden will be calculated as the total amount spent out-of-pocket as a proportion of annual household income.

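### Weekly work hours are averaged over 12 months at a visit only 6 months after scheduled surgery, so the 6-month change in hours is about half the true change

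*Protocol article*

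**What the plan says.** Under *Economic circumstances and health care utilisation*, employment status is a secondary outcome, and its hours measure has a fixed recall period: "The average number of hours of paid and unpaid work performed per week over the previous 12 months will be calculated". In Table 1, "Time spent doing paid work" and the matching unpaid-work item are ticked at all three visits.

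Under *6 and 12 month interviews*, follow-up takes place "six months and 12 months after the participant's scheduled date of surgery using a similar interview schedule to that administered at baseline". No different recall period is given for the 6-month visit.

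Income is described less exactly. Table 1 lists "Annual income" at all three visits, and the text says "Participants are also asked about annual income and whether they are receiving any income support payments". The 12-month period is implied by the word annual; it is not written as a look-back.

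Health spending is scaled by the same quantity: "The out-of-pocket burden will be calculated as the total amount spent out-of-pocket as a proportion of annual household income". No recall period is given for the spending itself.

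A separate follow-up item asks about return to work, in what capacity and for how many hours a week. In addition, "The date of return to partial or full-time work will be recorded".

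The *Statistical analysis* section promises a model for each secondary and tertiary outcome. It names return to work, change in household income and economic hardship as dichotomous outcomes for logistic regression, and it allows for repeated measures on each respondent.

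**The concern.** A 12-month average taken 6 months after surgery cannot be a post-surgery measure. It mixes six months with cataract and six months after the operation. It also shares months with the baseline window on one side and with the 12-month window on the other. The 6-month change in hours would therefore understate what surgery achieved. The rise from 6 to 12 months would be partly or wholly a product of the windows, and could be read as slow recovery of working capacity.

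Household economic circumstances are part of the primary aim in the *Overview*. Under *Statistical considerations* the sample is raised from 266 to 400 so that the secondary outcomes can be studied. The error also cannot be repaired afterwards: a single 12-month average cannot be split into its halves before and after surgery.

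**Working it through.** **Inputs.** Recall of 12 months (*Economic circumstances and health care utilisation*). Visits 6 and 12 months after scheduled surgery (*6 and 12 month interviews*). The article gives no expected change and no standard deviation for hours, so there is no figure of the plan to reproduce. Delay, ramp-up and noise values below are assumptions.

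**1. Share of the window after surgery.** Let v be the visit month and d the delay of actual surgery after the scheduled date. The window runs from v − 12 to v. With an immediate, constant effect D on weekly hours, the window average changes by D × (v − d)/12.

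| Delay d (assumed) | 6-month visit | 12-month visit | Apparent growth, 6 to 12 months |
|---|---|---|---|
| 0 months | 6/12 = 0.50 D | 12/12 = 1.00 D | 2.0-fold |
| 1 month | 5/12 = 0.42 D | 11/12 = 0.92 D | 2.2-fold |
| 2 months | 4/12 = 0.33 D | 10/12 = 0.83 D | 2.5-fold |
| 3 months | 3/12 = 0.25 D | 9/12 = 0.75 D | 3.0-fold |

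The true effect is constant after surgery in every row, so all the growth in the last column comes from the windows and the delay.

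**2. Gradual effect.** If the effect builds linearly over 3 months (assumed) after on-time surgery, the 6-month figure is (3 × 0.5 + 3 × 1)/12 = 4.5/12 = 0.375 D. A recall since surgery would give 4.5/6 = 0.75 D. The ratio of the two is again one half.

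**3. Overlap.** If the baseline interview falls close to the scheduled date, its window is about months -12 to 0. The 6-month window then shares months -6 to 0 with baseline and months 0 to 6 with the 12-month window.

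**4. Does the halving carry over to a dichotomised change?** Take independent half-year noise of SD 1 and add recall error of SD r at each interview (both assumed).

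- 12-month recall at 6 months: change D/2, with variance 0.5 + 2r².
- Recall since surgery: change D, with variance 1.5 + 2r².
- r = 0: 0.5/0.707 = 0.707 D against 1/1.225 = 0.816 D, ratio 0.87.
- r = 1: 0.5/1.581 = 0.316 D against 1/1.871 = 0.535 D, ratio 0.59.

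For D = 0.5, the gain in the probability of an increase is Φ(standardised change) − 0.5. This gives 0.138 against 0.158 when r = 0, and 0.063 against 0.105 when r = 1. Between about 60% and 87% of the contrast is kept, because noise in the shared months cancels. This range belongs to the assumptions, not to the protocol.

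**The case against.** The strongest reply is that the article ties the 12-month average to no particular visit, and promises a follow-up schedule that is similar to the baseline one, not identical. The questionnaire may use a shorter recall at 6 months. That is possible. But the article states one definition, applies the item at all three visits and gives no exception, so the rule as written yields the diluted value.

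A second reply is that the return-to-work item already captures current hours and has no 12-month recall. It does support the named return-to-work outcome, which this point leaves untouched. It has no baseline counterpart in Table 1, however, and it is not a clear substitute for people who kept working at reduced hours.

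A third is that a year-long recall averages over the farming seasons, which matters where 80% (Thai Binh) or 57% (Vinh Long) of the population are farmers. This stands as a reason for 12-month recall at baseline and at 12 months. It does not turn the 6-month value into a post-surgery one.

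Three stronger readings are tempting, and the document supports none of them.

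- **That every economic outcome is halved.** For income the look-back is only implied, and the modelled outcome is a dichotomous change, for which step 4 shows that halving does not follow.
- **That the out-of-pocket burden is biased towards no effect.** The spending recall is not stated, so the direction is unknown. A one-off cost at surgery, for example, would fall wholly inside a window from month -6 to +6.
- **That a power loss can be quoted.** The 4-point difference and SD of 17 belong to SF-12 physical functioning, not to hours. Halving the effect at a fixed SD would also ignore the noise shared with baseline.

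**Conclusion.** The point holds for weekly hours at the 6-month visit. The mean change is about half the true change, assuming on-time surgery, an immediate constant effect and the 12-month recall used as written. It is smaller still if surgery is late, and a constant benefit would appear to grow from 6 to 12 months. The 12-month window lies wholly after surgery when surgery is on schedule.

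For annual income in money terms the same dilution follows if annual means the preceding 12 months. For dichotomised income change its size is not established. For the out-of-pocket burden, what can be said is that at 6 months an annual denominator is paired with a numerator of unstated period.

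The SF-12 primary outcome is not affected. The article does not say that the 6- and 12-month values of these outcomes will be pooled into one effect, so bias in a pooled estimate should not be presumed.

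**What to change.** At the 6-month interview, ask about paid and unpaid hours, and income, since the scheduled date of surgery or over the past 6 months. Express them per week or per month so that they compare with baseline. State the recall period for out-of-pocket spending, and use income over the same period as its denominator.

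If the 12-month survey wording has to stay, base the surgery effect on these measures on the 12-month visit only, and do not read the 6-month value as a post-surgery result.

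The first option costs a change of recall wording, made before the 6-month interviews begin. Its downside is seasonality, since a half-year of farm work would be compared with a full-year baseline. Adjusting for calendar month and comparing with the concurrent non-surgical group would help, though that group is not randomised. The second option costs the 6-month result for these secondary outcomes.

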### Statistical analysis

For descriptive purposes, baseline characteristics will be presented for the surgical group (those who have had cataract surgery) and the non-surgical group (those who have not had surgery). Discrete variables will be summarised by frequencies and percentages. Continuous variables will be summarised by use of standard measures of central tendency and dispersion, including median and inter-quartile ranges given potential skewness in the data.

We will calculate mean changes in the SF-12v2 scores for the surgical and non-surgical participants at the six months and one year follow up points. Reductions in scores indicate deterioration and improvements in scores indicate an improvement in quality of life. Generalised linear models will be used to assess multivariate-adjusted mean differences in SF-12v2 scores comparing surgical and non-surgical participants.

To assess the impact of cataract surgery on household economic circumstances and psychological outcomes, models will be constructed based on each of the secondary and tertiary outcomes listed above. For the dichotomous outcomes, 'returned to work', change in household income and economic hardship, the models will be estimated through logistic regression. Household wealth and psychological impact, specified as continuous outcomes, will be modelled using parametric or non-parametric methods depending on the distributional characteristics of each outcome. The modelling will account for the potential random effects, as each individual respondent will yield multiple measures.

The cost-effectiveness analysis will take a societal perspective. The costs of surgery will be assessed through financial statements provided by Vietnam Blindness Prevention Program staff. These will include staff, travel and training costs associated with running the cataract surgery program, including the costs of the operations. Cost-offsets in terms of use of health care services and medications will be assessed based on individual self-report in the follow up interviews. Effectiveness will be assessed in terms of quality of life, using the SF-12v2, with incremental cost-effectiveness ratio estimated based on cost per quality adjusted life years.

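### Economic hardship can be scored on an unmet medical payment alone, so surgery forgone because of cost could fix both the group and the outcome and may bias the odds ratio in favour of surgery

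*Protocol article*

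**What the plan says.** In the protocol article, under Economic circumstances and health care utilisation, household economic hardship "will be determined by a series of questions about failure to pay basic living and medical expenses", together with whether anyone helped to meet those payments. The outcome is dichotomous: "a reported inability to make any one of the payments posed to respondents will be classed as a case of economic hardship". The same paragraph counts it as a strength that the measure notices households setting priorities among payments, and its example is that they "forgo medical expenses to pay school fees".

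Under Statistical analysis, the surgical and non-surgical groups are formed by whether the operation took place. The purpose is stated as follows: "To assess the impact of cataract surgery on household economic circumstances and psychological outcomes, models will be constructed" for each secondary and tertiary outcome. For hardship the method is given as: "For the dichotomous outcomes, 'returned to work', change in household income and economic hardship, the models will be estimated through logistic regression". Multivariate adjustment is mentioned for the SF-12v2 comparison; no covariates are named for the hardship model.

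Table 1 lists the hardship topics, including financial stress, at baseline, 6 months and 12 months. Follow-up is timed from the scheduled date of surgery (6 and 12 month interviews).

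**The concern.** Every participant has been referred for one particular medical service, and receiving it is the exposure. Medical expenses are among the hardship items, one failed payment is enough, and nothing in the article sets the cataract operation apart from other medical expenses. A household that goes without the operation because it cannot pay could therefore enter the non-surgical group and become a hardship case through the same event, with no other item failed.

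This overlap between exposure and outcome is distinct from ordinary confounding by poverty. It would lower the surgical versus non-surgical odds ratio even if restored vision did nothing for household finances. At stake is whether that odds ratio can be read as the impact of surgery on hardship, one of the secondary outcomes.

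**Working it through.** The article gives no hardship prevalence, patient charge, reason for non-uptake or item wording, so there is no figure of the plan's own to reproduce. The check asks how large the overlap could be under stated assumptions.

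**Inputs (all assumed)**
- *h*: prevalence of hardship from all other causes, equal in both groups (no true effect of surgery).
- *q*: share of otherwise unaffected non-surgical households that went without surgery because they could not pay.
- *s*: probability that the medical item records this.

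**Formulas**
- Surgical prevalence: *h*.
- Non-surgical prevalence: *p* = *h* + (1 − *h*) × *q* × *s*.
- Odds ratio, surgical versus non-surgical: [*h*/(1 − *h*)] / [*p*/(1 − *p*)].

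**Main illustration**, *h* = 0.30 and *s* = 1, so the surgical odds are 0.30/0.70 = 0.429:

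| *q* | *p* | Non-surgical odds | Odds ratio |
|---|---|---|---|
| 0.10 | 0.30 + 0.70 × 0.10 = 0.37 | 0.37/0.63 = 0.587 | 0.73 |
| 0.20 | 0.30 + 0.70 × 0.20 = 0.44 | 0.44/0.56 = 0.786 | 0.55 |
| 0.40 | 0.30 + 0.70 × 0.40 = 0.58 | 0.58/0.42 = 1.381 | 0.31 |

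The share *q* applies only to the 70% who are not already cases. As a share of all non-surgical households, the three rows add 7, 14 and 28 percentage points.

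**Range over the assumptions**, *h* from 0.20 to 0.60:
- *s* = 1: odds ratio 0.64 to 0.84 at *q* = 0.10, and 0.32 to 0.58 at *q* = 0.30.
- *s* = 0.5: odds ratio 0.79 to 0.92 at *q* = 0.10, and 0.53 to 0.77 at *q* = 0.30.
- *q* = 0 or *s* = 0: odds ratio 1.00.

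**Opposing effect.** If paying for surgery pushes a share *c* of otherwise unaffected surgical households into hardship, surgical prevalence becomes *h* + (1 − *h*) × *c*. With *s* = 1 the odds ratio is 1.00 when *c* = *q*. With *q* = 0.10 and *c* = 0.20 it is 1.20 (*h* = 0.60) to 1.45 (*h* = 0.20). The observed ratio can thus mix the overlap with a real cost of treatment.

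**Leaving the medical item out.** Scored on non-medical items alone, prevalence is the same in both groups under these assumptions, so the odds ratio is 1.00 whatever *q* and *s* are.

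**The case against.** A reader might infer that going without surgery and being a hardship case coincide by definition, and that surgery will look protective when it is not. The documents do not support that.

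- **Item wording.** Neither the wording nor the recall period of the medical item is shown. An item about bills that could not be paid would not count an operation that was never bought. The example of forgone medical expenses makes the overlap possible but does not prove it.
- **Charges.** The article places the costs of the operations in the programme's financial statements and does not say what outreach patients pay. Private recruits are described as people who elect to have surgery and are capped at one per outreach participant (Recruitment). Refusal because of cost may be uncommon.
- **Direction.** Hardship brought on by paying for the operation pushes the other way. It is a genuine effect of surgery, because Overview and Statistical analysis ask about the impact of surgery, not of restored vision alone. Removing it from the main outcome could itself flatter surgery.
- **Independence.** Households too poor to pay probably fail other items too, so the medical item would change fewer classifications than the illustration assumes. What remains is confounding by poverty, a separate matter.
- **Data already planned.** Baseline hardship is collected, and random effects for repeated measures are planned.

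The first four points stand as limits on certainty about whether the bias occurs, how large it is and which way the net result goes. They leave the structure untouched: the scoring rule and the grouping are both stated, and together they allow one event to determine both. The last point helps only in part. Failure to pay for the operation can arise after the baseline interview, so baseline adjustment cannot fully remove it, and random effects deal with correlation within a participant, not with this overlap.

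**Conclusion.** The concern holds in a conditional form. As scored, the hardship outcome may share an event with group membership, and this may bias the odds ratio towards surgery looking protective. The condition is that some participants forgo surgery because of cost and that the medical item records it. With no true effect and 30% background hardship, the spurious odds ratio would be 0.73, 0.55 or 0.31 for assumed shares of 10%, 20% or 40% of otherwise unaffected non-surgical households. It is 1.00 if surgery is not charged or forgone care is not covered. The article supplies none of these inputs.

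It does not follow that the net result must favour surgery, nor that a true benefit is absent. The supportable conclusion is narrower: a protective odds ratio on this outcome alone would not be sufficient evidence that surgery reduces household hardship.

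**What to change.** 1. Keep the any-one-payment outcome, medical item included, as the main version, so that hardship caused by paying for surgery is still counted.
2. Adjust its model for baseline hardship, which is already collected.
3. Pre-specify a second version scored on the non-medical living-expense items only, compared between the same groups with the same adjustment.
4. Claim a protective effect of surgery on hardship only if both versions agree, and state beforehand what counts as agreement.

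If the versions disagree, report both without attributing the gap to the overlap alone. The second version also drops other unmet medical costs, as well as any surgery-related hardship that shows only on the medical item. Neither version removes confounding by poverty.

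The cost is fewer cases, hence less precision, in the second version, and a little more analysis. The translated and piloted interview schedule need not change.
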